### Data analysis

A detailed Statistical Analysis Plan will be developed by the trial statistician (who is independent of the Sponsor) and agreed by the Trial Management Committee (TMC) before the analysis is undertaken. The analysis and presentation of results will follow the most up-to-date recommendations of the CONSORT group. Analyses will be completed in STATA® version 13.0 or later.

All analyses will follow the intention to treat principle, i.e. data from all randomised woman and babies will be analysed according to the treatment they were allocated to irrespective of the treatment they received or whether they received any treatment at all.

Blinding will not be possible for participants and care providers, because of the open nature of the interventions, nor will the DSMC be blinded to allocation in their assessment of outcomes and safety, but the outcome data will be blinded to the data analysts by concealing the group allocation prior to the analysis.

Demographic and clinical data will be summarised with counts and percentages for categorical variables, means (standard deviations) for normally distributed continuous variables and medians (with interquartile or simple ranges) for other continuous variables.

For the primary outcome, the effectiveness of the interventions will be assessed by calculating the differences in mean pruritus score with 95% confidence intervals (CI), determined with a linear regression model, using Generalised Estimating Equations (GEEs).

All comparative analyses will be performed adjusting for stratification variables and baseline measures of the outcome, where relevant. Binary outcomes will be analysed using log binomial regression models. Results will be presented as adjusted risk ratios plus 95% CIs. If the model is unstable, log Poisson regression models with robust variance estimation will be used [34]. Continuous outcomes will be analysed using linear regression models, and results will be presented as adjusted differences in means (with 95% CIs). Analysis of outcomes that are measured repeatedly over time (severity of pruritus and biochemical markers) will use repeated measures analysis techniques, including GEEs and/or random effects.

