## Methods/design

### Trial hypotheses

The primary trial hypothesis is that rifampicin, compared with UDCA treatment of women with severe early onset ICP, commenced between 14^+ 0^ and 33^+ 6^ weeks of gestation, reduces the degree of pruritus, measured as worst itch in the previous 24 h assessed on a patient-recorded visual analogue scale.

Secondary trial hypotheses include:
Rifampicin, compared with UDCA, improves short-term outcomes for both mother and infant in severe early onset ICP, including the length of gestation and the incidence of caesarean section and preterm birth.Rifampicin, compared with UDCA, improves markers of maternal liver function in severe early onset ICP, including serum BA and serum transaminase concentrations.

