## Interventions

The intervention under test is rifampicin (rifampicin) tablets 300 mg twice daily and the comparator treatment is ursodeoxycholic acid (UDCA) tablets up to 2000 mg daily, prescribed as per the usual local protocols.

Women meeting the inclusion criteria and consenting to participation will be randomly allocated to treatment with rifampicin or UDCA at study entry. The duration of treatment will range from 1 day to a maximum of 28 weeks, for a participant randomised at 14 weeks who does not deliver until 42 weeks.

Within the trial, both UDCA and rifampicin are usually dispensed by the local hospital pharmacy.

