### Randomisation

Initial random allocation to treatment with rifampicin or UDCA will be in a ratio of 1:1.

Randomisation is managed via a secure web-based randomisation facility hosted on REDCap at The University of Adelaide, with telephone back-up available.

Stratification is by centre and by severity (serum BA concentration prior to randomisation < 100 μmol/L, ≥100 μmol/L).

The woman is allocated a unique participant identification number on randomisation.

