## Statistics

### Rationale for sample size

One hundred eight women are required to have a 90% chance of detecting, as significant at the 5% level, a decrease in maternal pruritus score from -16 mm in the UDCA group to -23 mm in the rifampicin group, (with a standard deviation (SD) of 10 mm across both arms, allowing for a 5% drop out in each arm).

The SD stipulated for the sample size calculation might appear to be too small, on the basis of the values reported in the PITCH study, in which UDCA reduced itching by -16 mm (95% confidence interval -27 mm to -6 mm) [27].. The estimate and 95% Confidence Interval for the difference in pruritus score between the UDCA and the Placebo group was -16 mm (-26.5,  -5.9 mm). This suggests that the standard error is approximately 5.3 mm, and hence the standard deviation of the difference between the groups (given *n* = 55 and *n* = 56) is approximately 28 mm.

The statistical power of the study, however, has been calculated with the intended sample size of 108 (*n* = 54 per group), so as to detect a difference between UDCA and rifampicin if the mean change in pruritus score in the UDCA group is -16 mm (as reported in the PITCH study versus placebo, where change in the placebo group was negligible), while the mean change in pruritus score in the rifampicin group is -30 mm (which has already been stipulated as the minimum change that would be considered clinically meaningful). These calculations were done as the power for a simple comparison of two means, and via simulation to allow for up to five measurements per participant, with correlation between the repeated measures, and show that there is approximately 75% power (with two-sided alpha 0.05) to detect a difference between the groups of this magnitude; i.e., if rifampicin achieves a clinically meaningful reduction in pruritus score while UDCA achieves a reduction of the magnitude reported in PITCH, there is 75% power to detect this.

In the recent PITCHES study, however, the reduction of pruritus score in the UDCA group was much more modest (-5.7 mm) [14]. The CI gives a very similar SD, i.e. 25 mm. This gives much greater power to detect a difference between UDCA and rifampicin: if rifampicin had a change of -23 mm, we have approx. 95% power, and if it had a mean change of -30 mm, > 99% power.

The inclusion of multiple centres will enable maximum recruitment over a limited time scale.

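### Gestation at randomisation is not named as a covariate for days from randomisation to birth, an outcome it enters by subtraction, so precision may be lost needlessly

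*Protocol article*

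**What the plan says.** The Data analysis section of the protocol article gives one covariate rule for every comparison: "All comparative analyses will be performed adjusting for stratification variables and baseline measures of the outcome, where relevant". For continuous outcomes it adds: "Continuous outcomes will be analysed using linear regression models, and results will be presented as adjusted differences in means". The Randomisation section supplies the strata: "Stratification is by centre and by severity", with severity split at a serum bile acid concentration of 100 μmol/L. The pre-specified subgroups use the same two factors. Gestation at entry is not named as a stratum, a covariate or a subgroup.

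The Inclusion criteria admit women from 14+0 to 33+6 weeks, dated by ultrasound. The Interventions section shows how far the time to birth can vary as a result: "The duration of treatment will range from 1 day to a maximum of 28 weeks". Days from randomisation to birth and gestation at birth are listed separately among the secondary maternal outcomes. One of the secondary hypotheses concerns short-term outcomes, "including the length of gestation and the incidence of caesarean section and preterm birth".

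**The concern.** Days from randomisation to birth is an arithmetic difference: gestation at birth minus gestation at entry. A woman randomised at 16 weeks will almost always have a longer interval than one randomised at 33 weeks, whatever drug she receives. The outcome has no value at baseline, so a literal reading of the rule leaves it adjusted for centre and bile acid stratum only, and not for the quantity subtracted to form it.

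Two things follow. The confidence interval may be much wider than the data require. And the plan lists two outcomes that both bear on length of gestation; before covariates, their treatment differences differ by exactly the chance imbalance in entry gestation. The report could therefore show two different answers to nearly the same question, for a reason unrelated to treatment.

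**Working it through.** **Inputs.** The documents give no precision or power figure for any gestation outcome, so there is no figure of the plan's own to reproduce. From the Rationale for sample size I take 54 women per arm. From the Inclusion criteria I take the entry window: 20 weeks, or 140 days. The SD of gestation at entry (s_E), the SD of gestation at birth (s_B) and their correlation (r) are not in the documents. They are assumptions, varied below. Centre and bile acid stratum are left out of the calculation; if they predict entry gestation, the gain is somewhat smaller.

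**Formulas.**
- Variance of the interval without entry gestation in the model: s_E² + s_B² − 2·r·s_E·s_B.
- Residual variance with it in the model: s_B²·(1 − r²).
- Standard error of the treatment difference: SD × √(2/54) = SD × 0.1925.
- The proportion of variance removed does not depend on the number of women.

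**Results for days from randomisation to birth, r = 0.** Uniform entry over 140 days gives s_E = 140/√12 = 40.4 days.

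| s_E (days) | s_B (days) | Interval SD | SE without | SE with | Variance removed |
|---|---|---|---|---|---|
| 19.6 (mostly late entry) | 10.5 | 22.2 | 4.3 | 2.0 | 78% |
| 40.4 (uniform) | 10.5 | 41.8 | 8.0 | 2.0 | 94% |
| 14 | 14 | 19.8 | 3.8 | 2.7 | 50% |
| 21 | 14 | 25.2 | 4.9 | 2.7 | 69% |
| 40.4 (uniform) | 14 | 42.8 | 8.2 | 2.7 | 89% |

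First row in full: √(19.6² + 10.5²) = 22.2; 22.2 × 0.1925 = 4.3; with adjustment, 10.5 × 0.1925 = 2.0; variance removed 19.6²/(19.6² + 10.5²) = 384/494 = 78%. The 95% half-width (1.96 × SE) falls from 8.4 to 4.0 days.

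A simulation of 2,000 trials of 108 women, with a birth SD of 14 days, agrees. The standard errors without and with entry gestation were 8.20 and 2.66 days (uniform entry), 4.89 and 2.65 (entry SD about 21 days), and 3.82 and 2.61 (entry SD about 15 days).

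**Where the gain shrinks.** A positive correlation reduces it. With s_E = s_B = 14 days, the variance removed falls from 50% at r = 0 to 40% at r = 0.2 and 25% at r = 0.5. The least favourable case tried was s_E = 14, s_B = 21, r = 0.5:
- without adjustment: 196 + 441 − 294 = 343;
- with adjustment: 441 × 0.75 = 330.75;
- variance removed: 1 − 330.75/343 = 4%.

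**Gestation at birth.** Entry gestation is not part of this outcome, so adjustment removes only r²: 0% at r = 0, 9% at r = 0.3 and 25% at r = 0.5. At r = 0.5 the standard error is multiplied by √0.75 = 0.87, a fall of 13%.

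**Chance imbalance.** The SE of the between-arm difference in mean entry gestation is 19.6 × 0.1925 = 3.8 days for mostly late entry and 40.4 × 0.1925 = 7.8 days for uniform entry. An imbalance of at least 7 days in either direction is 1.86 or 0.90 standard errors, with probability of about 6% or 37%. A 7-day imbalance moves the unadjusted difference in days to birth by 7 days relative to the unadjusted difference in gestation at birth.

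**Agreement of the two outcomes.** In a linear model, subtracting a covariate from the outcome changes only that covariate's own coefficient. With entry gestation and the same other covariates in both models, fitted to the same women, the treatment estimates for days to birth and gestation at birth are identical.

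**The case against.** The strongest reply is that this belongs to the statistical analysis plan. The article announces one ("A detailed Statistical Analysis Plan will be developed by the trial statistician"), it is not shown, and the covariates for one of many secondary outcomes are the sort of detail an article leaves to it. The rule is also not closed: it does not say that nothing else may be added, and its qualifier about relevance could be read to make entry gestation the baseline measure for a gestational outcome. This stands in part. The plan may already include the covariate, and nothing in the article forbids it. But the article is not silent: it states a rule for all comparisons, and that rule taken literally omits the variable. In an open-label trial a covariate is better named in advance than chosen later.

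A reader might infer more than the documents support:
- **That all gestation outcomes lose most of their precision.** They do not. Gestation at birth forgoes only r² of its variance.
- **That the length-of-gestation hypothesis cannot be answered.** Gestation at birth is a listed outcome, measures it directly and does not carry the entry variance.
- **That the estimate is biased by who entered early.** Randomisation keeps it unbiased, and the unadjusted standard error already allows for chance imbalance.
- **That the itch analysis suffers.** Entry gestation affects how many itch scores a woman gives and when, but that does not show that a covariate would help. No gain has been shown for itch, preterm birth, mode of birth, birth weight or neonatal stay.

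**Conclusion.** The point holds for one secondary outcome, days from randomisation to birth. With 54 per arm, a birth SD of 10 to 14 days, an entry SD of 14 to 40 days and no entry-birth correlation, adjusting for gestation at randomisation removes about 50% to 94% of the variance of the treatment estimate. The gain falls as the correlation rises, to about 4% in the least favourable case tried.

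All these SDs and correlations are assumptions. The article gives some reason to expect births to cluster: its Current practice section describes delivery in severe disease as often brought forward to 36 to 37 weeks, and its Background says many centres aim for birth by 37 weeks. Entry, by contrast, is open over 20 weeks. That favours the larger gains but does not establish them.

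The cost of leaving the rule as it is would be avoidable imprecision and possible disagreement between two related outcomes. Validity is not at stake, and no effect on the primary outcome is shown. This is a free improvement, not an error that threatens the trial.

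**What to change.** In the analysis section, and in the statistical analysis plan if it is not already there, name gestational age at randomisation, as a continuous variable, as a covariate in the linear model for days from randomisation to birth. Name it also in the linear model for gestation at birth, with the same other covariates, so that the two treatment estimates agree. The rule for other outcomes need not change on this evidence.

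The cost is one phrase and one degree of freedom in each model. No new data are needed, because eligibility already requires ultrasound-dated gestation.

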## Background

Intrahepatic cholestasis of pregnancy (ICP) is the most frequent liver disorder specific to pregnancy, with an annual Australian incidence of 0.6–0.8% [1]. Its cardinal features are maternal pruritus and increased serum bile acids (BA), commonly towards the end of the third trimester. The pruritus, though often mild, can occasionally be extremely severe, causing major skin excoriations, profound sleep disturbances and associated psychopathology, with iatrogenic premature delivery for symptom relief. ICP can also cause severe liver dysfunction and jaundice. BA are formed in the liver and secreted in the bile into the intestine, where they emulsify fat in the ingested food and enable its uptake into the liver, where the BA are recycled. In ICP, this cycle of “enterohepatic circulation” is inhibited and serum BA concentrations increase, providing a marker for the disorder [2]. Increased rates of postpartum haemorrhage (PPH) reported in early studies [3] have not been confirmed in more recent larger datasets [4]. Gallstones may be present more often in these women [5]. Women with hepatitis C infection have a higher incidence of ICP [6]. Maternal symptoms typically resolve after birth, but affected women have an increased risk of hepatobiliary disease in later life [6]. There are few data for long term outcome in the children of mothers with ICP [7].

ICP has been associated with increased fetal risks, including spontaneous preterm birth, fetal hypoxia and compromise (including meconium-stained liquor) and unexpected intrauterine fetal death [3]. Higher concentrations of circulating BAs are associated with increased fetal risks, including spontaneous preterm birth, asphyxial events and stillbirth [8, 9]. Early onset (less than 34 weeks gestation) severe (defined as serum BA > 40 μmol/L) ICP is a rare disorder with an Australian incidence of 0.1% per annum [1].

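### Days to resolution of symptoms falls under the linear-regression rule, which has no valid value for women who give birth with symptoms unresolved

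*Protocol article*

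**What the plan says.** The Data analysis section sets the models for the comparative analyses. For binary outcomes, "Binary outcomes will be analysed using log binomial regression models", with a Poisson fallback. For continuous outcomes, "Continuous outcomes will be analysed using linear regression models", reported as adjusted mean differences. For serial data, "Analysis of outcomes that are measured repeatedly over time (severity of pruritus and biochemical markers) will use repeated measures analysis techniques". No time-to-event method is named. The same section requires data from all randomised women to be analysed as allocated, and adjustment for the stratification variables and, where relevant, the baseline value. It defers detail to a later plan: "A detailed Statistical Analysis Plan will be developed by the trial statistician".

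The Secondary outcomes section lists days to resolution or amelioration of symptoms. It lists time to resolution after birth as a separate item.

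On the length of observation, the Interventions section says "The duration of treatment will range from 1 day to a maximum of 28 weeks". On what birth does to the outcome, the Background says "Maternal symptoms typically resolve after birth".

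**The concern.** Days to resolution is a waiting time that birth can interrupt. It is neither binary nor a repeated measure, so among the stated classes it can only be treated as continuous. A woman who gives birth still itching has no day of resolution before birth, and a linear model needs a number for her or must leave her out.

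Leaving her out selects women on something that happened after randomisation and breaks the intention-to-treat rule. Entering her birth day records a non-event as an event. In both cases the arm with slower resolution loses or shortens more of its long times, so the arms look more alike than they are. At stake is a secondary efficacy result that speaks directly to symptom relief.

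**Working it through.** The article gives no figure for this outcome, so there is none to reproduce. The check has two parts.

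**1. Does the article itself imply women unresolved at birth?** Yes.
- Resolution after birth is listed as its own outcome, which would be empty if every woman resolved beforehand.
- Windows can be short. Entry is allowed up to 33 weeks 6 days (237 days). The Current practice section says delivery in severe disease is often brought forward to 36 to 37 weeks (252 to 259 days). For the latest entrants that leaves 252 − 237 = 15 to 259 − 237 = 22 days.
- The sample-size section works with mean changes of −5.7 to −30 mm on a 100 mm scale, so complete resolution before birth cannot be presumed for all.

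**2. How much would linear regression lose?** All inputs here are assumptions: exponential resolution time with median m, a true rate ratio of 2 in favour of rifampicin, and birth uniform between *lo* and *hi* days after entry, alike in both arms and independent of resolution time.

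Formulas, with λ = ln 2 / m:
- True mean = 1/λ.
- Unresolved at birth: S = (e^(−λ·lo) − e^(−λ·hi)) / (λ(hi − lo)).
- Mean with birth day substituted = (1 − S)/λ.
- Mean with unresolved women dropped = 1/λ − E[B·e^(−λB)]/(1 − S), where B is the birth day.

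Worked case: birth at 28 to 84 days, medians 42 (UDCA) v 21 (rifampicin).
- True means 60.6 v 30.3, difference 30.3 days.
- UDCA: S = (0.630 − 0.250)/0.924 = 0.411. Rifampicin: S = (0.397 − 0.0625)/1.848 = 0.181.
- Substituted: 60.6 × 0.589 = 35.7 v 30.3 × 0.819 = 24.8, difference 10.9 days, or 36% of the true difference.
- Dropped: 24.5 v 19.7, difference 4.7 days (from unrounded means), or 16%.

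All nine scenarios (differences in days; share of the true difference in brackets):

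| Birth, days | Medians | Unresolved | True | Substituted | Dropped |
|---|---|---|---|---|---|
| 14–42 | 84 v 42 | 80% v 64% | 60.6 | 2.7 (4%) | 0.75 (1%) |
| 14–42 | 42 v 21 | 64% v 41% | 30.3 | 4.2 (14%) | 1.4 (5%) |
| 14–42 | 28 v 14 | 51% v 27% | 20.2 | 5.1 (25%) | 1.9 (10%) |
| 28–84 | 84 v 42 | 64% v 41% | 60.6 | 8.5 (14%) | 2.8 (5%) |
| 28–84 | 42 v 21 | 41% v 18% | 30.3 | 10.9 (36%) | 4.7 (16%) |
| 28–84 | 28 v 14 | 27% v 8% | 20.2 | 11.0 (54%) | 5.9 (29%) |
| 56–154 | 84 v 42 | 43% v 20% | 60.6 | 20.2 (33%) | 8.3 (14%) |
| 56–154 | 42 v 21 | 20% v 5% | 30.3 | 19.8 (65%) | 11.7 (39%) |
| 56–154 | 28 v 14 | 9% v 1% | 20.2 | 16.7 (82%) | 12.2 (60%) |

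A simulation of the same scenarios agrees to within 0.1 day.

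**Censoring at birth instead.** The event rate is the proportion resolved divided by mean time observed: (1 − S) / ((1 − S)/λ) = λ. The unresolved fraction cancels, so the rate ratio is 2 in every row; the simulation returned 2.00 to 2.01.

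**The case against.** *The allocation to linear regression is inferred, and the SAP may set a censoring rule.* Partly stands. The sentence on continuous outcomes does not name this outcome, and the SAP is not shown. But the section does more than stay silent: it states a rule for continuous outcomes, and a count of days falls under it. An SAP that follows the article would inherit the problem.

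*The outcome is not said to stop at birth.* True. If follow-up ran on, women unresolved at birth would mostly resolve soon afterwards because they had given birth. Their value would be roughly the birth day, which is close to the substitution case, and it would overlap with the separate outcome of resolution after birth.

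*The substituted difference has a meaning.* It does: it is the difference in mean symptomatic days before birth. That is a legitimate quantity if declared, but it is not days to resolution, and it also moves with time to birth. The secondary hypotheses expect rifampicin to improve short-term outcomes "including the length of gestation and the incidence of caesarean section and preterm birth".

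*Amelioration is a lower bar than resolution, so few women may be unresolved.* This stands as a limit on size. The last row of the table shows the loss is modest when 9% v 1% are unresolved and birth is substituted.

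*A reader might extend the point to peak bile acids up to delivery.* The documents do not support that. The peak is observed in any woman sampled after entry, and the randomised comparison of peaks to delivery is valid for that outcome. Length of gestation arises after randomisation, so it is not a baseline confounder. If gestation is equal between arms there is no distortion. Serial bile acids are already assigned a repeated-measures analysis.

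**Conclusion.** The point holds for days to resolution or amelioration of symptoms. The stated model classes include none suited to it, and the rule it falls under has no valid value for women who give birth unresolved. Dropping them or substituting the birth day pulls the difference towards zero: 1% to 60% of the true difference is kept in the first case and 4% to 82% in the second.

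These ranges rest wholly on assumed resolution times and birth windows. A reader might infer that the effect will be badly underestimated; that is not established, because the article does not give the unresolved fraction and the loss can be modest. A reader might also infer that the result could point the wrong way; that is not shown, since every scenario kept the right sign. The exact recovery of the rate ratio assumes that birth is unrelated to the time of resolution. The outcome is one of many secondary outcomes, and the primary pruritus analysis is untouched.

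**What to change.** In the Data analysis section, except this outcome from the linear-regression rule and analyse it as time to event from randomisation:
- a cause-specific Cox model that censors at birth, adjusted for centre, bile acid stratum and baseline itch;
- cumulative incidence curves by arm, with birth as a competing event.

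Keep resolution after birth as the separate outcome already listed.

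The cost is a change of wording; no new data are needed. The result becomes a hazard ratio with cumulative incidence instead of a difference in mean days. If delivery is brought forward because symptoms persist, the hazard ratio describes women still pregnant and symptomatic, so it should be read together with the cumulative incidence curves.
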